#### Analytic plan for secondary outcomes

We propose common mechanisms (i.e., motivation, agency, and stress/negative affect) on smoking abstinence for both the MAPS + and ST treatments, but potential for differences in the relative strength of each mechanism by group. These prospective differences will be assessed via mediation analyses with intervention as the independent variable, abstinence as the outcome variable, and the hypothesized mechanisms (motivation, agency, stress/negative affect) as mediators. Whereas 24 months is the final assessment point, abstinence at earlier assessments will also be evaluated in order to capture points in time when transitions from smoking to abstinence are more likely. To assess mediation effects, we will fit both single and multiple mediator models, using the approaches of MacKinnon [78] and Preacher and Hayes,[79–81] as appropriate.

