This paper describes the research design, methods, and data analysis plans for an ongoing randomized clinical trial (RCT) designed to evaluate the efficacy of MAPS + in facilitating smoking cessation among survivors of CIN or cervical cancer. The primary aim of the trial is to compare the efficacy of MAPS + in facilitating smoking cessation with standard treatment (ST). A secondary aim is to evaluate motivation for smoking cessation, agency, and stress/negative affect as prospective mediators of the difference in abstinence between the MAPS + and ST treatment groups. Whereas each is a likely mechanism for both interventions, the relative importance may differ. For example, higher levels of quit motivation may mediate abstinence in ST, whereas higher levels of agency may mediate abstinence in MAPS+.

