### Statistical analysis

#### Analytic plan for primary outcome

Logistic regression will assess treatment group differences in self-reported 7-day point prevalence abstinence at 24 months. Generalized estimating equations (GEE) will fit population-averaged models of longitudinally measured self-reported 7-day point prevalence abstinence, with the main covariates of treatment group, time (months from baseline), and the interaction of group and time. The GEE analysis permits evaluation of aggregated intervention effects across assessments, changes in abstinence over time, and group differences in changes (interaction term). These models will include any covariates found to differ by group (p < .10) despite randomization. Comparable models will be applied to evaluate treatment differences for secondary outcomes.

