### Power and sample size

The primary statistical analyses will evaluate intervention effects on 7-day point prevalence abstinence. This will be done in two ways: (1) using logistic regression at 24 months, and (2) using GEE to assess intervention effects aggregating across all assessments. Based on results from our recently completed trial [15], abstinence rates in both groups are expected to increase over time along with an increasing difference between groups. Estimated abstinence at 24 months is 16% for ST and 29% in MAPS+. PASS 2020 [85] was used to estimate sample size/power for logistic regression analyses. With a sample size of 170 per group, power is ≥ 0.80 for logistic regression analyses at 24 months with alpha = 0.05 and a two-sided test. Using GEESIZE 3.1, [86] power ≥ 0.95 for GEE analysis of abstinence across all follow-ups. No adjustments to enrollment size will be needed to account for attrition as we will utilize multiple imputation to manage missing data.

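### The mediation models as described have no treatment-by-mediator term, so they cannot show whether a mechanism matters more in one arm than in the other

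*Protocol article*

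**What the plan says.** The secondary aim, given at the end of the protocol article's background (MAPS + overview and rationale), is to evaluate motivation, agency and stress/negative affect "as prospective mediators of the difference in abstinence between the MAPS + and ST treatment groups". The text then adds that the importance of each may not be the same in the two arms, with the example that "higher levels of quit motivation may mediate abstinence in ST, whereas higher levels of agency may mediate abstinence in MAPS" (that is, in MAPS+).

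The analytic plan for secondary outcomes takes this up. It proposes mechanisms common to both arms, with "potential for differences in the relative strength of each mechanism by group". The next sentence assigns that question to a model: "These prospective differences will be assessed via mediation analyses with intervention as the independent variable, abstinence as the outcome variable", with the three constructs as mediators. On model form it says "we will fit both single and multiple mediator models", following cited mediation approaches as appropriate.

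The only interaction named anywhere in the article is "the interaction of group and time", in the GEE for abstinence. The only modelling within one arm is of engagement measures in MAPS+, and it does not involve these mediators.

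**The concern.** The text asks two questions. The first is which mediators carry the difference in abstinence between the arms. The second is whether a given mediator is more strongly tied to abstinence in one arm than in the other. The second is about effect modification: the slope of abstinence on the mediator would have to differ by arm. A mediation model in which arm enters only as the independent variable fixes that slope to be equal in both arms, so it produces no estimate of the quantity that the text says it will assess.

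The risk lies in interpretation. If motivation matters mainly under quitline treatment and agency mainly under MAPS+, the model reports an intermediate slope for each, with nothing to show where it operates. A by-arm statement about mechanism in the trial report would then have no estimate behind it.

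**Working it through.** **The plan's own figure.** The article gives no power for the mediation analysis. The nearest figure is for the primary outcome: "Estimated abstinence at 24 months is 16% for ST and 29% in MAPS" (MAPS+), and "With a sample size of 170 per group, power is ≥ 0.80 for logistic regression analyses at 24 months". It reproduces at two-sided alpha 0.05:

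- Pooled two-proportion test: mean proportion (0.16 + 0.29)/2 = 0.225. Null SE = √(2 × 0.225 × 0.775/170) = 0.0453. Alternative SE = √((0.16 × 0.84 + 0.29 × 0.71)/170) = 0.0447. z = (0.13 − 1.96 × 0.0453)/0.0447 = 0.92, so power is 0.82.
- Wald test on the log odds ratio: power 0.81.

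This confirms the design inputs but does not bear on the mediation question.

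**Structure of the stated model.** With T = arm (0 = ST, 1 = MAPS+), M = mediator and Y = abstinence:

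- M = i₁ + a·T + error
- logit P(Y = 1) = i₂ + c′·T + b·M
- indirect effect on the log-odds scale = a·b

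There is one b per mediator. A multiple mediator model adds more mediators, each again with one b. Comparing a·b across mediators shows which carries more of the between-arm difference, not in which arm any of them works.

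**Structure needed for the by-arm question.**

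- logit P(Y = 1) = i₂ + c′·T + b_ST·M + d·T·M
- b_MAPS+ = b_ST + d, and d = 0 is the hypothesis of equal strength.

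**Simulation inputs.** None of these effect values is in the article: one mediator with SD 1, a = 0.3, direct effect c′ = 0.5 log-odds, intercept −1.8, and slopes that are equal or differ by arm. The simulated abstinence rates were 14% to 17% in ST and 22% to 29% in MAPS+, against the planned 16% and 29%.

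**Bias check (400,000 per arm).**

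| True b, ST / MAPS+ | Shared b | a·b | Interaction model: b in ST | Interaction model: b in MAPS+ |
|---|---|---|---|---|
| 0.5 / 0.5 | 0.50 | 0.15 | 0.50 | 0.50 |
| 0.9 / 0.1 | 0.43 | 0.13 | 0.89 | 0.10 |
| 0.1 / 0.9 | 0.56 | 0.17 | 0.10 | 0.90 |

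Equal slopes and two opposite patterns all give a shared slope between 0.43 and 0.56 and an indirect effect between 0.13 and 0.17. Nothing in that output tells the three situations apart. In the second row the arm-specific products are 0.3 × 0.9 = 0.27 using the ST slope and 0.3 × 0.1 = 0.03 using the MAPS+ slope, where the stated model reports 0.13.

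**Power for the interaction (170 per arm, complete data, 1,000 runs, two-sided 0.05).**

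| True b, ST / MAPS+ | Proportion with p < 0.05 |
|---|---|
| 0.5 / 0.5 | 0.054 (type I error) |
| 0.3 / 0.7 | 0.25 |
| 0.1 / 0.9 | 0.76 |

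The term is correctly calibrated, but it detects a moderate difference in slopes only about one time in four.

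**The case against.** **The aim can be answered.** A reader might infer that the whole secondary aim fails. The documents do not support that. The aim as worded concerns mediators of the between-arm difference, and a model with arm as the independent variable addresses it. The motivation-versus-agency sentence is an illustration that follows the aim. This objection stands and limits the point to the by-arm question.

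**Silence is not exclusion.** The article prints no model equation and does not declare equal slopes. It leaves room by saying that the cited approaches will be used as appropriate, and a full analysis plan might add an interaction. This stands in part. However, the article goes beyond leaving the method open: it poses the by-group question and in the next sentence names the analysis that will answer it, with arm in one role only. That assignment needs correcting whatever a later document adds.

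**By-group differences could mean differences in mediator level.** If ST raised motivation more and MAPS+ raised agency more, the treatment-to-mediator paths would show it. That is true, but it concerns how far each treatment moves a mediator, not how strongly the mediator is tied to abstinence within each arm.

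**Timing.** A reader might infer from the shared follow-up schedule in Table 1 that mediators and abstinence will be paired at the same visit, so that having quit could itself raise self-efficacy. The article never says so. Earlier mediator values exist at the preceding follow-ups, and some constructs are also measured every 30 days in both arms. What remains is that the pairing is not fixed.

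**The example has no numbers.** A reader might take it to mean that a mediator has no effect at all in the other arm. The plan proposes common mechanisms that differ in relative strength, so a zero slope would be an assumed extreme. The slopes used in the working are assumptions too.

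**Conclusion.** The point holds for the by-arm question only. As described, each mediator has one path to abstinence common to both arms, and no treatment-by-mediator term or arm-stratified mediator model appears elsewhere. This is structural and does not depend on the simulation. The simulation only illustrates the consequence: under the assumed values, opposite arm patterns give shared slopes of 0.43 and 0.56, while the interaction model returns the arm-specific slopes to within about 0.01.

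The power figures of about 0.25 and 0.76 depend on the assumed slopes and on complete data, and missing data would lower them. The importance is moderate. It affects what can be claimed about mechanism in a secondary analysis and leaves the primary efficacy comparison untouched.

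**What to change.** Choose one of two courses.

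1. **Keep the by-arm question.** Add treatment-by-mediator terms to the outcome model. Report the mediator slope in each arm, the corresponding indirect effects and the interaction, all with confidence intervals. Label this analysis exploratory, and state that a non-significant interaction is not evidence that mechanisms are the same.
2. **Drop it.** Reword the sentence in the analytic plan for secondary outcomes so that the question is mediation of the between-arm difference only, which the stated models already address.

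Under either course, fix the timing: take each mediator from an assessment that precedes the abstinence outcome (for example month 3 or 6 for abstinence at month 12 or later) and adjust for its baseline value. Do not combine natural indirect effects with adjustment for abstinence reached after randomisation. That variable is itself affected by treatment, and natural effects are then generally not identified.

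The cost is a few lines of wording and some extra modelling, with no new data. Under the first course, the imputation model must also allow mediator–abstinence associations to differ by arm (for example by imputing within arm), or the interaction will be diluted. The price is lower precision for the interaction than for a shared slope.

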#### MAPS + evaluation

Engagement measures (e.g., number of counseling calls completed, amount of text-based treatment content received) initially will be evaluated via descriptive statistics. These variables also will be explored as predictors of smoking abstinence. First, univariate logistic regression analyses will be used to identify prospective predictors. Univariate significant predictors will be submitted to a multivariable model with backward stepwise procedures to identify the set of predictors that make a unique contribution to abstinence in the MAPS + condition.

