### General analytic approach

We hypothesize that self-reported 7-day point prevalence abstinence rates will be greater in MAPS + than in ST. All data analyses will be performed using SAS version 9.4 with significance set at 0.05 for statistical tests of primary hypotheses. Descriptive statistics will be used for initial review of distributions and determination of needs for transformation prior to primary analyses. Group differences in baseline measures will be assessed and any variable that exhibits a group difference at p < .10 will be added as a covariate in the primary analyses.

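### The exploratory MAPS+ engagement analysis selects predictors by univariate significance and then backward steps in one arm, so the surviving odds ratios are overstated and their p-values ignore the selection

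*Protocol article*

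**What the plan says.** The MAPS + evaluation section of the protocol article starts from engagement measures and names two by way of example: "Engagement measures (e.g., number of counseling calls completed, amount of text-based treatment content received". They are first described, and then: "These variables also will be explored as predictors of smoking abstinence".

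The method has two steps. "First, univariate logistic regression analyses will be used to identify prospective predictors". After that, "Univariate significant predictors will be submitted to a multivariable model with backward stepwise procedures". The stated aim is to "identify the set of predictors that make a unique contribution to abstinence in the MAPS + condition".

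The section gives no p-value threshold for either step, no full candidate list, no engagement window and no abstinence time point. General analytic approach has "significance set at 0.05 for statistical tests of primary hypotheses", which does not formally cover this analysis.

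Three points elsewhere in the article bear on it:
- Calls are delivered over the first 12 months and texts over all 24 (Intervention conditions).
- Call timing may change when a participant has trouble staying abstinent (Intervention conditions), and text content is matched to current smoking status (Intervention conditions; Smoking abstinence).
- Abstinence is assessed at 3, 6, 12, 18 and 24 months (Procedures).

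**The concern.** The selection method is fixed in the text, so this is not a detail left open. A predictor enters the multivariable model only if its univariate p-value is small, and stays only if its adjusted p-value is small. The model then reports odds ratios and p-values as though nothing had been selected. With few events, a moderate effect survives mainly in those samples where chance has made it look larger. Where measures are correlated, as calls and texts going to the same people may be, the procedure can keep the wrong one. It is therefore poorly suited to showing a unique contribution.

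A second problem concerns direction. Texts continue up to the 24-month assessment. If people who are abstinent engage more (or less), text engagement totalled over 24 months can be associated with 24-month abstinence without influencing it.

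What is at stake is how the components of MAPS+ are described afterwards: a short list of predictors with inflated odds ratios. The test of whether MAPS+ works is not at stake.

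**Working it through.** **Inputs from the documents.** 170 per group; "Estimated abstinence at 24 months is 16% for ST and 29% in MAPS"+; "alpha = 0.05 and a two-sided test". The article gives no figure for the engagement analysis, so the only figure to reproduce is the power statement that uses the same inputs.

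**Reproducing that figure.** The pooled proportion is 0.225.
- Null SE = √(2 × 0.225 × 0.775 / 170) = 0.0453.
- Alternative SE = √((0.16 × 0.84 + 0.29 × 0.71) / 170) = 0.0447.
- z = (0.13 − 1.96 × 0.0453) / 0.0447 = 0.92, so power is 0.82. The Wald log-odds-ratio version gives 0.81. The stated power of at least 0.80 is confirmed.

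**Events.** 0.29 × 170 = 49.3 expected abstainers in MAPS+, or about 5 coefficients at ten events each.

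**Assumptions.** A threshold of 0.05 at both steps; normally distributed, equally correlated candidates; complete data; 2 to 10 candidates.

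**Overstatement, closed form for one standardised predictor.**
- SE ≈ 1/√(170 × 0.29 × 0.71) = 1/√35.0 = 0.169.
- The estimate must exceed about 1.96 × 0.169 = 0.331 to be selected.
- For a true log odds ratio of 0.35, the cut lies (0.331 − 0.35)/0.169 = −0.11 SE from the truth. The chance of selection is Φ(0.11) ≈ 0.54.
- Mean estimate when selected ≈ 0.35 + 0.169 × φ(0.11)/0.54 = 0.35 + 0.12 = 0.47.

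Simulating the full two-step procedure gives about 0.50, because the realised SE is slightly larger and the logistic estimate has a small upward bias. An odds ratio of e^0.35 = 1.42 is thus reported as about e^0.50 = 1.65. The mean stays near 0.50 with 1, 2, 4 or 6 candidates and correlations from 0 to 0.6, so it does not depend on the unstated candidate count. The true predictor is retained in about 36 to 53% of trials, least often with more and more strongly correlated candidates.

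**False retention when no measure matters.** For k independent measures the chance of at least one false univariate pass is 1 − 0.95^k. Simulated rates for the full procedure (2,000 trials per setting, correlation 0.5 to 0) are alongside.

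| Candidates | 1 − 0.95^k | Simulated, at least one retained |
|---|---|---|
| 2 | 9.75% | 8–9% |
| 4 | 18.5% | 15–19% |
| 6 | 26.5% | 20–27% |
| 8 | 33.7% | 25–33% |
| 10 | 40.1% | 27–40% |

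Repeat runs differ by a point or two (26–39% for ten, for example).

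**Wrong predictor retained.** With one true predictor (odds ratio 1.6 per SD) and correlation 0.8, a null measure is retained in 15%, 31% and 48% of trials with 2, 4 and 8 candidates. The true one is retained in 65%, 52% and 39%.

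**Direction, illustration only.** Assume monthly smoking status with a 4.5% chance of quitting and a 9% chance of relapse (about 32% abstinent at month 24), 60% monthly engagement while smoking, and no effect of engagement on abstinence. If abstinence raises the odds of engaging 1.5-, 2- or 3-fold, engagement totalled over months 0–24 is significant for 24-month abstinence in 34%, 70% and 93% of trials. Counting months 0–12 only, the figures are 6%, 8% and 9%. These show the mechanism. They do not estimate its size in this trial.

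**The case against.** The case on the other side is substantial, and most of it stands as a limit on the point.

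- **Exploratory and confined to one arm.** The article says the measures will be explored, and the analysis feeds no other. This stands and sets the severity. It does not rescue the method, because the stated output is a selected set with a unique contribution.
- **How often the findings are chance.** A reader might infer that the named predictors will often be chance findings. The documents do not support that: only two measures are named, the total is not given, and with two the all-null rate is 8 to 10%. Rates above 25% need roughly six to ten candidates.
- **Same-period measurement.** A reader might infer that engagement and abstinence are measured over the same period. The article does not say so. It fits texts against 24-month abstinence and calls against abstinence at 3 to 12 months. It is untrue of calls against 24-month abstinence, because calls end by month 12, although early abstinence could still influence both.
- **Size of reverse causation.** Any figure rests on assumed inputs. The article's one link between abstinence and calls concerns people who are struggling, which could push the association the other way. The number of texts sent largely follows a schedule; smoking status tailors their content. The risk is real, but its size is unknown.
- **Missing detail.** Windows, thresholds and the candidate list may sit in an analysis plan that is not shown, so their absence is not held against the article. A fuller plan could add them, but it could not make the screen and backward steps sound without replacing them.
- **Consequence.** A reader might infer that the selected set will steer dissemination. The Discussion ties dissemination to MAPS+ being efficacious, not to which measures survive selection.

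**Conclusion.** The point holds as a low-severity criticism of a stated method. Selecting engagement predictors by univariate significance and then backward steps, with about 49 events, overstates the effects that survive: about 0.50 for a true 0.35 on the log-odds scale. It misses a true effect of that size in roughly half to two thirds of trials. False retention is modest with the two named measures and rises to about 26 to 40% with ten.

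These results assume 0.05 at both steps, the planned 29% abstinence, complete data and normally distributed candidates. The inflation result does not depend on the candidate count; the false-retention result does. For texts totalled to month 24, the direction of any association cannot be established, and the documents give no basis for sizing the problem. The primary, secondary and mediation analyses are unaffected.

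**What to change.** Replace the univariate screen and backward steps with the following:

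1. Prespecify a short list of engagement measures and fit them together in one logistic model with baseline predictors. With about 49 events, the list should be short. If a test is wanted, one joint test at 0.05 keeps the all-null false-finding rate at 5% whatever the number of measures.
2. For the main engagement model, measure engagement in a window that ends before the outcome, for example months 0–12 for month-24 abstinence.
3. Adjust for month-12 smoking status only as a sensitivity analysis. Calls run to month 12, so that status may lie on the path from calls to later abstinence. In a simulation where calls acted only through quitting by month 12 (assumed log odds ratio 0.5 to 1.0 per SD; 70% v 14% abstinent at month 24 by month-12 status), power was 32 to 79% without the adjustment and 4 to 6% with it.
4. Report every estimate with its confidence interval, retained or not, and label all of them as associations.

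The cost is wording and a different model, with no new data. The downsides are wider intervals, no final set of predictors, and texts in months 13–24 that are described but not modelled in the landmark analysis.

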### Missing data management

To manage missing data, multiple imputation under the Missing at Random assumption will be applied using a Markov Chain Monte Carlo method [82] via PROC MI in SAS version 9.4 given the expected large numbers of non-monotonic missing data patterns and auxiliary variables (e.g., baseline measures that predict smoking status) identified via preliminary analyses. Twenty data sets will be created. For smoking status, a post hoc adjustment [83] will be applied to implement an influence of Missing Not at Random (MNAR) (i.e., missing is due to smoking). In recent publications, [84] we have applied a small-medium effect size (Cohen’s *d* = 0.35). This approach provides better parameter estimates and tests of hypotheses than does imputing missing equals smoking. Sensitivity analyses will be performed by systematically increasing the MNAR influence in *d* = 0.15 increments to the point of missing equals smoking.

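### Fixing the number of imputations at twenty leaves avoidable Monte Carlo noise in the 24-month p-value; raising it is a minor improvement at almost no cost

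*Protocol article*

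**What the plan says.** Under Missing data management, the article states that "multiple imputation under the Missing at Random assumption will be applied using a Markov Chain Monte Carlo method". It explains the choice of method: "given the expected large numbers of non-monotonic missing data patterns and auxiliary variables". It then fixes the number: "Twenty data sets will be created". Smoking status also receives a post hoc not-at-random adjustment, for which earlier work used d = 0.35. Further, "Sensitivity analyses will be performed by systematically increasing the MNAR influence", in steps of d = 0.15, until every missing status counts as smoking.

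General analytic approach has "significance set at 0.05 for statistical tests of primary hypotheses". Power and sample size gives the design values: "Estimated abstinence at 24 months is 16% for ST and 29% in MAPS"+, with 170 per group, and "power is ≥ 0.80 for logistic regression analyses at 24 months with alpha = 0.05 and a two-sided test". That section makes no allowance for attrition and relies on multiple imputation instead. No section states an expected missing rate or FMI.

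**The concern.** A pooled estimate from a finite number of imputations carries simulation error on top of sampling error. Twenty imputations keep that error small relative to the standard error, which is what matters for estimation. A p-value read against a fixed threshold is more sensitive: when the result lies near 0.05, a small shift in the test statistic changes the verdict. Two analysts with the same data and the same plan, but different seeds, could then report different conclusions. The number is a stated choice in the article, and a larger one costs almost nothing.

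**Working it through.** **Inputs.** From the article: m = 20 imputations, 170 per group, 16% against 29% abstinent at 24 months, two-sided 0.05. Assumed, because the article gives no figure: FMI from 0.1 to 0.4.

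**1. The plan's own figure.** The log odds ratio is ln[(0.29/0.71)/(0.16/0.84)] = 0.763. Its standard error is √[1/(170 × 0.16 × 0.84) + 1/(170 × 0.29 × 0.71)] = 0.269. The expected z is 0.763/0.269 = 2.84, so power is 0.81 (Wald test); a two-proportion test gives 0.82. The stated power of at least 0.80 reproduces, for complete data.

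**2. Efficiency.** Relative to unlimited imputations, efficiency is 1/(1 + FMI/m). At m = 20 this is 1/1.005 = 0.995 for FMI 0.1 and 1/1.02 = 0.980 for FMI 0.4. The loss is at most about 2%.

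**3. Noise in the test statistic.** The Monte Carlo standard deviation of the pooled estimate, in units of its standard error, is about √(FMI/m). At m = 20 it is 0.07, 0.10, 0.12 and 0.14 for FMI 0.1, 0.2, 0.3 and 0.4. At m = 200 and FMI 0.2 it is √(0.2/200) = 0.032.

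**4. A result near the boundary.** Take a result whose p-value with unlimited imputations (the limiting p) is 0.04, so z = 2.054. It clears 1.960 by 0.094. At FMI 0.2 and m = 20 that margin is 0.094/0.10 = 0.94 Monte Carlo standard deviations, so noise in the estimate alone would lose significance for about 17% of seeds. Allowing also for noise in the between-imputation variance and for Rubin's degrees of freedom raises this to about 25%. Full results by simulation of Rubin's rules:

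| FMI | 95% range of p over seeds, m = 20 | Non-significant, m = 20 | m = 100 | m = 200 |
|---|---|---|---|---|
| 0.1 | 0.028–0.058 | 13% | 0.4% | under 0.1% |
| 0.2 | 0.023–0.071 | 25% | 4% | 1% |
| 0.3 | 0.019–0.084 | 33% | 10% | 3% |
| 0.4 | 0.016–0.097 | 38% | 15% | 7% |

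The limiting p is held at 0.04 in every row, so the trend reflects FMI alone.

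A direct check imputed one fixed data set within arm, with 170 per arm, 30% missing (assumed) and a limiting p of about 0.042. Over seeds, p ran from 0.020 to 0.085 at m = 20, with 63% of seeds below 0.05. At m = 100 it ran from 0.031 to 0.058, with 85% below 0.05.

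**5. How often this would matter.** Step 4 is conditional on a borderline result. The unconditional figure is the chance that two seeds disagree at 0.05 when the design alternative is true:

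| FMI | m = 20 | m = 100 | m = 200 |
|---|---|---|---|
| 0.1 | 2.7% | 1.2% | 0.9% |
| 0.2 | 4.7% | 2.0% | 1.5% |
| 0.3 | 6.7% | 2.9% | 2.1% |
| 0.4 | 8.6% | 3.7% | 2.7% |

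Power at m = 20 is below power at m = 100 by 0.5 points at FMI 0.1 (0.764 against 0.769) and 1.5 points at FMI 0.4 (0.577 against 0.592). The much larger fall from 0.81 comes from the missing information itself, and more imputations do not recover it.

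**6. Clear results.** At a limiting p of 0.01, more than 99% of seeds stay below 0.05 at m = 20 for every FMI up to 0.4.

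**7. The graded series.** If each step were imputed afresh, the difference between two neighbouring steps would carry noise of about √2 × √(FMI/m). At FMI 0.2 and m = 20 that is 1.41 × 0.10 = 0.14 in z. If the same imputed sets are reused, much of that noise is common to the steps and cancels from their comparison.

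**The case against.** The strongest reply is that twenty is neither an error nor a contradiction. Bias is unaffected, the efficiency loss is negligible and clear results do not move. All of that stands, and it is why the point is minor.

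Four stronger readings are tempting, and the article supports none of them.

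- **That much data will be missing.** The text says "given the expected large numbers of non-monotonic missing data patterns", and it says so to justify the method. With five follow-ups, even modest intermittent missingness produces many patterns. Monte Carlo error depends on FMI, not on the number of patterns. The planned auxiliary variables and the earlier smoking assessments may also lower FMI, so the direct check in step 4, which used no predictors, probably overstates the noise for a given missing rate.
- **That a borderline primary result is likely.** With a normal test statistic, the chance of p between 0.04 and 0.05 is about 2.6% at power 0.82 and 3.5% at power 0.67. The disagreement rates in step 5 are the fair summary; the 13% to 38% applies only once the result is already near the threshold.
- **That every step of the graded series carries the same noise.** The adjustment is described as post hoc, which suggests reuse of the imputed sets. At the last step every missing status is set to smoking, so imputation noise in the outcome vanishes.
- **That the absence of a seed or a Monte Carlo error report is a defect.** A condensed article commonly leaves both to the analysis plan. A pre-set seed would make the result repeatable, but the result would still reflect one arbitrary draw.

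It is also true that no finite number cures a result exactly on the boundary: at a limiting p of 0.05, about half of the seeds fall on each side even at m = 200. A larger number narrows the zone in which the seed decides but does not remove it.

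**Conclusion.** The point holds as a minor improvement in reproducibility. With FMI between 0.1 and 0.4, which is an assumption, raising the number of imputations from 20 to 200 cuts the chance that the seed decides the 24-month verdict by about two thirds, from 2.7–8.6% to 0.9–2.7% under the design alternative. It adds at most about 1.5 points of power. If little is missing at 24 months, the gain lies at or below the lower end of these ranges. The calculation supports no claim of bias or of an invalid analysis.

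**What to change.** In Missing data management, replace twenty by at least 100, preferably 200, imputed data sets. State that the graded not-at-random adjustments are applied to those same sets, so that differences between steps reflect the adjustment and not fresh random draws. The change is one number and one sentence, plus a few minutes of run time for 340 participants. It alters neither the imputation method nor the model or the estimand.
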